### Evaluation of adherence

2.16

Adherence will be measured at 4, 8 and 12 weeks via online questionnaires. For both groups, participants will provide information regarding the average number of hours per day and number of days they have worn the shoe inserts (arch contouring foot orthoses or sham inserts) and their shoes in the last 4 weeks. The average time spent wearing shoe inserts when in their shoes will then be calculated [35]. Participants will be classified as adherent if they wear their shoe inserts for an average of at least 35 h per week. To minimise participant burden, adherence will be documented on the day with recall over the previous 4 weeks rather than daily entry surveys [51, 52, 53].

### Adverse events

2.17

Adverse events relating to the use of interventions in both groups will be documented as the number of participants experiencing any adverse event (serious events and non‐serious events) and the number of participant withdrawals due to adverse events. Adverse events will be assessed at 4 week intervals via online questionnaires. Participants will be asked to document the type of adverse event, the body location, the frequency and/or the severity of the effect [48]. All reported adverse events will be reviewed by an independent assessor at the end of the trial and categorised as events that are *unrelated, probably related* or *definitely related*. Those considered to be *probably related* or *definitely related* will be considered an adverse event [54]. Serious adverse events will be defined as events that are life‐threatening, require hospitalisation or result in persistent or significant disability or incapacity [55]. If participants experience a severe adverse event (e.g. severe pain), they will be asked to contact one of the investigators.

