### Blinding

2.8

Participants will be blinded to group allocation by limited disclosure. Participants will be advised that the clinical trial has been designed to compare one of two types of shoe inserts for midfoot OA, but they will not be informed about the specific characteristics of the interventions. Due to the nature of the intervention (i.e. foot orthoses), research staff administering them cannot be blinded. The interventions will be referred to as ‘shoe inserts’ throughout the study and both groups will receive the same clinical guideline‐based information and support at the start of the trial. Primary and secondary outcomes are participant‐reported, thus this trial will also be considered assessor‐blinded (as participants are blinded). Trial personnel entering participant‐reported data and the biostatistician performing the statistical analyses for the trial will be blinded.

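### The adverse event comparison counts only events judged probably or definitely related, with no level for possible relation and no stated comparison of all reported events

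*Protocol article*

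**What the plan says.** Section 2.17 (Adverse events) opens with "Adverse events relating to the use of interventions in both groups" and gives two measures: "the number of participants experiencing any adverse event", covering serious and non-serious events, and "the number of participant withdrawals due to adverse events". On collection it says: "Adverse events will be assessed at 4 week intervals via online questionnaires". Participants give the type, body location, frequency and/or severity of each event.

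Classification follows: "All reported adverse events will be reviewed by an independent assessor at the end of the trial". There are three levels (unrelated, probably related, definitely related), and only events in the upper two "will be considered an adverse event".

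Section 2.20 (Statistical analysis) treats adverse event frequency as a dichotomous outcome, compared by relative risk, risk difference and number needed to treat. Section 2.8 (Blinding) covers participants and data-entry personnel and adds that "the biostatistician performing the statistical analyses for the trial will be blinded". It does not mention the adverse event assessor, who is described in section 2.17 only as independent.

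**The concern.** The counting rule makes causality part of the definition of an adverse event. As written, a reported event judged unrelated leaves the count, even if it meets the definition of a serious event. Read literally, the rule also governs withdrawals due to adverse events.

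A randomised comparison does not need this step. Background events should occur at the same rate in both arms apart from chance, so the difference between arms estimates the harm due to the orthoses. Filtering first puts a case-by-case judgement where randomisation already gives the answer.

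The scale makes that judgement harder. With no level between unrelated and probably related, each uncertain event has to be dropped or upgraded, and no rule says which.

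At stake is the harms comparison in a trial that the abstract says will help to inform clinical guidelines. The primary pain analysis and the sample size are not affected.

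**Working it through.** **Inputs.** The plan gives no adverse event rate and no figure on this point, so every rate below is an assumption. The one planned number used is 70 per arm (section 2.19), which reproduces: n = 2(1.960 + 0.842)² × 2.2²/1.1² = 2 × 7.849 × 4 = 62.8, rounded up to 63 per arm; 63/0.9 = 70; total 140. Tests are two-sided at 0.05.

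**Step 1. Equal attribution in both arms.** Let p₁ and p₀ be the proportions with any reported event (orthoses, sham) and s the share of those participants still counted after the filter.

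- RR = s·p₁/(s·p₀) = p₁/p₀, unchanged.
- RD = s(p₁ − p₀), shrunk by s. Its inverse, the number needed to treat, grows by 1/s.
- Power = Φ{[|RD| − 1.96√(2p̄(1−p̄)/n)] / √([p₁(1−p₁)+p₀(1−p₀)]/n)}, with the filtered proportions put in and p̄ their mean.

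With 30% against 15% assumed and s = 1: (0.15 − 1.96 × 0.0706)/0.0694 = 0.168, and Φ(0.168) = 57%. For other shares:

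| s | Counted | RD (points) | 1/RD | RR | Power |
|---|---|---|---|---|---|
| 1 | 30% v 15% | 15.0 | 6.7 | 2.0 | 57% |
| 0.75 | 22.5% v 11.25% | 11.25 | 8.9 | 2.0 | 43% |
| 0.50 | 15% v 7.5% | 7.5 | 13.3 | 2.0 | 29% |
| 0.25 | 7.5% v 3.75% | 3.75 | 26.7 | 2.0 | 16% |

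Other assumed rates behave alike. Going from s = 1 to s = 0.5, power falls from 74% to 38% at 40% v 20%, and from 65% to 35% at 25% v 10%.

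The same in counts, with SE(log RR) = √(1/a − 1/70 + 1/b − 1/70):

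- 20/70 v 10/70: SE 0.348, RR 2.0 (95% CI 1.01 to 3.96).
- Half removed in each arm, 10/70 v 5/70: SE 0.521, RR 2.0 (0.72 to 5.55).

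This is loss of precision and of absolute difference. It is not bias in the RR.

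**Step 2. Unequal attribution, no true difference.** Assume 30% in both arms report an event.

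- Attributed 75% v 50%: 22.5% v 15%, RR 1.5, chance of a significant result about 20%.
- Attributed 75% v 25%: 22.5% v 7.5%, RR 3.0, chance about 70%.

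Here the filter alone produces the difference.

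**Step 3. The favourable case.** Suppose 8 of the participants counted in each arm had only background events and the assessor removes exactly those: 20/70 v 10/70 becomes 12/70 v 2/70. RD stays at 10/70 = 14.3 points. RR rises to 6.0, with SE √(1/12 + 1/2 − 2/70) = 0.745 and 95% CI about 1.4 to 25.8. Accurate attribution that works alike in both arms would sharpen the contrast.

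**The case against.** The strongest defence is that attribution is a legitimate way to remove noise. Step 3 shows it can help, no documented rate favours dilution over sharpening, and the article cites a source for its rule that is not available here. This stands against any claim that the filter must do harm. It does not justify making the filtered count the only stated comparison, because the benefit depends on accurate judgement on a scale that cannot record uncertainty.

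Four stronger readings are tempting, and the documents do not support them.

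- *That review comes too late to act on, above all for serious events.* The end-of-trial step classifies events for analysis and is not the only safety route. Events are collected every 4 weeks, and after a severe event participants are told that "they will be asked to contact one of the investigators". Section 2.12 and the Discussion leave contact open throughout. Review of serious events during the trial may be described in the full protocol, so its absence from a journal article is no finding.
- *That the assessor is unblinded.* Blinding of the assessor is unstated, not shown to be absent. Because the sham lacks heel and arch support (section 2.10.2), the type and body location of an event could hint at allocation, but that is a possibility only.
- *That participants report only insert-related events, so there are two filters.* The opening phrase of section 2.17 describes what is documented, not what the questionnaire asks. An unrelated category implies that such reports are expected.
- *That the stated measure flatly contradicts the counting rule.* The word any may mean any related event, given the subject of its sentence. The tension is worth clearing up, but the point does not depend on it.

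**Conclusion.** The point holds as a weakness in how the harms comparison is fixed. Only events judged probably or definitely related count, possible relation has no place on the scale, and the arms are compared on that filtered count with no comparison of all reported events stated. The filter can dilute a real difference or, if attribution differs by arm, manufacture one.

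The size is unknown. The percentages in the working show direction under assumed rates, 70 per arm and a participant-level filter; they are not estimates for this trial. Adverse events are a secondary outcome and the trial was sized on pain, so limited power for harms is expected either way. This is a worthwhile, inexpensive improvement and does not threaten the trial's main conclusion.

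**What to change.** In sections 2.17 and 2.20:

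1. Compare by arm the number of participants with any reported adverse event, serious and non-serious, regardless of attribution, using the relative risk and risk difference already planned.
2. Present related events by arm in a separate table.
3. Add a possibly related level for uncertain events and count it with the related ones.
4. State that the assessor classifies events without access to allocation.

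The questionnaires already supply the data, and the same assessor can do the classification at the planned time, so no extra staff or visits are needed and the sample size is unchanged. Since classification is due only at the end of the trial, the changes can be recorded before it starts even though recruitment is under way. The downside is larger, noisier event counts that include background events in both arms; the separate table of related events lets readers see both.

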### Data management

2.18

Enrolment, baseline and follow‐up questionnaire data will be stored in REDCap™ and subsequently stored as electronic files on the La Trobe University secure server. Hardcopy versions of pain diagrams will be stored in a locked filing cabinet at La Trobe University and then shredded after being transferred into electronic formats for analysis (Microsoft Excel; Microsoft Corporation, USA and IBM SPSS Statistics; IBM Corporation, USA).

### Sample size

2.19

An a priori sample size calculation was conducted using G*Power version 3.1.9.7 [56, 57]. Using an allocation ratio of 1:1, power of 80%, assuming a minimal clinically important difference of 1.1 points [20] (representing a medium effect size [Cohen's *d*] of 0.5), standard deviation of 2.2 points [20], alpha set at 0.05 and allowing a 10% participant loss to follow‐up [20], a sample size of at least 140 participants (i.e. approximately 70 per group) will be required.

### Statistical analysis

2.20

Statistical analysis will be performed using the most recent version of SPSS available to the researchers using the intention‐to‐treat principle for all randomised participants. In participants with bilateral symptoms, the more painful side will be analysed (or the right lower limb if they cannot decide which is the more painful side) to maintain independence of data [58]. Standard tests to assess continuous data for normal distribution will be used. If continuous data is not normally distributed, transformation will be carried out if appropriate. Multiple imputation will be used to replace any missing data using five iterations, with sex, age, baseline scores and group allocation as predictors [59]. The exception will be for the GROC scale, co‐interventions, adherence and adverse events where no data substitution will be applied.

The primary outcome measure will be NRS pain measured at 12 weeks. To avoid over‐testing and to minimise the risk of type I error associated with serial measurements, statistical analysis of the efficacy of the interventions will specifically focus on the between group difference at 12 weeks [60, 61]. Differences in the primary and secondary outcome measures between the two groups will be compared. Continuously scaled outcome measures will be analysed using the analysis of covariance (ANCOVA) with baseline scores and intervention group entered as independent variables [62, 63]. Dichotomous outcome measures (e.g. frequency of adverse events, frequency of co‐interventions and dichotomised GROC) will be compared using relative risk, risk difference and number needed to treat. Intervention adherence will be compared using independent group *t*‐tests. For all analyses, both 95% confidence intervals and *p*‐values will be generated where appropriate.

A sensitivity analysis will be conducted to estimate treatment effects on the primary outcome. We will assess the robustness of the results from our analyses using the following conditions: (i) complete case analysis—only analyse participants who provide outcome data and (ii) last observation carried forward. A sensitivity analysis will also be undertaken to estimate treatment effects on the primary outcome assuming full adherence (per‐protocol analysis) [64]. Full adherence will be defined as participants reporting wearing the shoe inserts for an average of at least 35 h per week.

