### Participants

2.3

One hundred and forty participants will be recruited. To be eligible for inclusion, participants must: (i) be aged ≥18 years, (ii) have pain in the midfoot joints (located in at least one area in a predetermined dorsal midfoot region [26]) for at least 3 months that is aggravated by weight‐bearing activities, (iii) have pain in the midfoot when walking during the last 7 days that is rated an average of at least 3 out of 10 in severity on an 11‐point numerical rating scale (NRS) (where 0 represents ‘no pain’ and 10 represents the ‘worst pain imaginable’), (iv) have radiographic evidence of midfoot OA (defined in this trial as a minimum score of 1 for either observations of joint space narrowing or osteophytes in at least one of the midfoot joints in either radiographic view) assessed using the La Trobe University Atlas of Foot OA [27], (v) be able to walk household distances (more than 50 m) without the aid of a walker, crutches or cane, (vi) be willing to regularly wear shoes that will accommodate shoe inserts, and (vii) be willing to attempt to not use co‐interventions (including pain relieving oral medications) during the study period.

Participants will not be eligible for inclusion if they: (i) have had previous ipsilateral foot surgery or are planning surgery in the next 12 weeks, (ii) have OA secondary to other issues such as major trauma, (iii) have the presence of other foot or ankle condition(s) or have pain in another location that is greater than the pain in the midfoot, (iv) have any musculoskeletal or systemic medical conditions (e.g. suspected inflammatory joint disease or neurological conditions) that could make them unsuitable for inclusion or confound pain and functional assessments of the midfoot, (v) are unable to speak and read English, (vi) have had treatment that includes the use of any foot orthoses (including shock absorption shoe inserts), ankle braces and/or, received intra‐articular injections at the midfoot in the previous 12 weeks, and (vii) have dementia or any cognitive impairment.

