#### Pain

2.13.1

The primary outcome is average pain in the midfoot whilst walking in the last 7 days scored using an 11‐point NRS with terminal descriptors of 0 (‘no pain’) and 10 (‘worst pain imaginable’). This outcome measure has been used as a primary outcome measure in a feasibility trial that investigated arch contouring foot orthoses for midfoot OA [35] and has been recommended for clinical trials in OA [40]. Although there are no studies that have assessed the responsiveness of the NRS specifically in midfoot OA, the NRS has been shown to be more responsive, easier to administer and preferred by adults compared to other pain scales [41]. In people with chronic musculoskeletal pain, the minimal clinically important difference of the NRS has been reported to be between 1 and 2 points [42, 43].

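### The test-then-transform rule in section 2.20 does not exempt the primary pain score, so it could take the primary estimate off the points scale on which the 1.1-point difference is defined

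*Protocol article*

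**What the plan says.** Section 2.20 (Statistical analysis) sets two linked rules. The check is: "Standard tests to assess continuous data for normal distribution will be used". The consequence is: "If continuous data is not normally distributed, transformation will be carried out if appropriate". No test, threshold, transformation or back-transformation is named. The check is directed at the data and makes no mention of model residuals.

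The same section then gives the model: "Continuously scaled outcome measures will be analysed using the analysis of covariance (ANCOVA) with baseline scores and intervention group entered as independent variables". The primary outcome falls under it, and nothing takes that outcome out of the transformation rule. Section 2.13.1 (Pain) defines it: "The primary outcome is average pain in the midfoot whilst walking in the last 7 days scored using an" 11-point scale from 0 to 10.

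The yardsticks for the result are in points of that scale. Section 2.19 (Sample size) proceeds by "assuming a minimal clinically important difference of 1.1 points" with a "standard deviation of 2.2 points". Section 2.13.1 puts the minimal clinically important difference at between 1 and 2 points.

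**The concern.** ANCOVA asks for roughly normal residuals, or enough participants for the adjusted mean difference to behave well. It does not ask for normal raw scores. A whole-number score with a floor and a ceiling is not normal, and at this sample size a formal test will detect that whether or not the model is in trouble. The trigger therefore says little about the validity of the analysis that it governs.

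If the analyst then transforms, the primary effect becomes a ratio or a difference in roots. It can no longer be set against 1.1 points or the range of 1 to 2 points. The choice is made after the outcome data are seen and against no stated criterion. What is at stake is the scale, and so the clinical reading, of the primary result.

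**Working it through.** **1. Inputs.** From section 2.19: difference 1.1, SD 2.2, power 80%, "alpha set at 0.05", allocation 1:1, loss 10%, total 140. From section 2.3: baseline pain "rated an average of at least 3 out of 10 in severity". Assumed, because the protocol does not give them: control mean at 12 weeks of 3, 4 or 5; SD of 1.8 to 2.5 around the stated 2.2; baseline mean 5.5 and SD 1.8, cut at 3; baseline-outcome correlation 0.4. Sidedness is not stated and is taken as two-sided.

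**2. The plan's own figure.** n per arm = 2 × (1.96 + 0.84)² × 2.2² / 1.1² ≈ 62.8, rounded up to 63. Total 126, and 126 / 0.9 = 140, as stated. The t-based version gives 64 per arm and 128 / 0.9 = 142.2, so 143, close to 140. A one-sided test would give 114, which supports the two-sided reading. The sample size is sound, and about 126 participants would have 12-week data.

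**3. How often the trigger fires.** Scores were drawn from a normal distribution, rounded and clipped to 0–10, with 63 per arm, a 1.1-point effect and 1,000 replicates per setting. The table shows the percentage of trials with p < 0.05 for non-normality at SD 2.2 (SW = Shapiro-Wilk; KS = Kolmogorov-Smirnov with Lilliefors correction).

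| Control mean | Pooled raw, SW / KS | Either arm raw, SW / KS | ANCOVA residuals, SW / KS |
|---|---|---|---|
| 5 | 100 / 100 | 76.4 / 95.1 | 6.4 / 10.2 |
| 4 | 100 / 100 | 99.9 / 98.4 | 17.8 / 17.2 |
| 3 | 100 / 100 | 100 / 100 | 58.5 / 46.6 |

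Over SDs of 1.8 to 2.5 the ranges are: pooled 100% (SW) and 99 to 100% (KS); either arm 76 to 100% and 88 to 100%; residuals 5 to 72% and 9 to 59%. Rounding alone is enough: at mean 5 and SD 2.2, a sample of 126 with no group effect was rejected in 100% by both tests, against 38% (SW) and 79% (KS) in a single arm of 63.

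**4. Whether transforming helps.** At SD 2.2, Shapiro-Wilk still rejected in 100% of pooled samples after log(x+1) or square root, at every mean. Mean skewness:

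| Control mean | Raw | log(x+1) | Square root |
|---|---|---|---|
| 5 | 0.08 | −1.23 | −1.10 |
| 4 | 0.25 | −0.91 | −0.91 |
| 3 | 0.50 | −0.48 | −0.54 |

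At means of 4 and 5 the shape gets worse. At 3 the skew changes sign and keeps about the same size.

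**5. Whether the untransformed model needs rescue.** With 20,000 replicates per setting, its two-sided type I error was 4.9% with scores mid-scale and 4.7% near the floor. A separate run over control means 3 to 5 gave 4.6 to 5.8%, with power of 83 to 85% against 82% on log(x+1).

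**6. What 1.1 points becomes.** On log(x+1) it is ln(m + 1) − ln(m − 0.1), where m is the control mean. For m = 3: ln 4 − ln 2.9 = 0.32. For m = 4, 5 and 6: 0.25, 0.20 and 0.17. On the square root, √m − √(m − 1.1) gives 0.35, 0.30, 0.26 and 0.24. No single transformed value corresponds to the planned difference. Because a score of 0 is possible, a log also needs an added constant, which the plan does not name.

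**The case against.** The strongest reply is that the sentence leaves transformation to the analyst's judgement of whether it is suitable. Keeping the score in points also complies with the rule, and step 4 gives good reason to keep it. This stands. A reader might infer that the plan will move the primary effect off the points scale; the text supports only that it could.

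The near-certain rejection belongs to pooled raw scores. It is weaker within one arm and does not carry over to residuals. That also stands, although the sentence speaks of data and not of residuals.

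The entry threshold of 3 might be read as making the 12-week outcome non-normal. It restricts baseline pain, which is a covariate whose distribution ANCOVA does not constrain, so it adds nothing to the case.

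A reader might also suspect that the scale could be chosen to favour one arm. Section 2.8 (Blinding) has the biostatistician blinded, which guards against that. Blinding does not, however, fix the scale in advance or restore the comparison with 1.1 points.

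The inferential loss is small: 82% power against 83 to 85%, with no inflation of type I error shown. The harm is to interpretation.

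Finally, an article condenses a fuller protocol, and diagnostic detail may sit there or in an analysis plan. That would answer a complaint about an omission. Here a rule is stated, it covers the primary outcome, and it is poorly aimed as written.

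**Conclusion.** The point holds in a limited form. Applied to pooled raw pain scores, the check rejects in practically every trial of this size whether or not ANCOVA is valid, and the transformations tried do not cure what it detects. The rule leaves open, with no criterion, whether the primary effect is reported in points. Using that latitude would cut the link to the 1.1-point difference and the 1-to-2-point range, and would gain nothing in type I error or power.

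The percentages depend on the assumed means, SDs and baseline distribution and on a single correlation of 0.4. The pooled raw-score result is stable across the means and SDs tried; the residual result is not, and rises as scores approach the floor. The loss of the points scale under any non-linear transformation needs no simulation.

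The figures do not show that robust or bootstrap intervals are required, since ordinary ANCOVA already kept its error rate near 5%. They do not touch the sample size. The weakness merits correction but does not invalidate the trial.

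**What to change.** For the primary outcome, replace the test-then-transform rule with: *The 12-week pain NRS will be analysed untransformed by ANCOVA and reported as an adjusted mean difference in NRS points with 95% CI; model residuals will be inspected, and any transformation or robust/bootstrap method will be a sensitivity analysis only.*

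The cost is one sentence. The model, the covariate and the total of 140 stay as they are. HC3 or bootstrap intervals are optional; if wanted, the plan should say how they combine with the multiple imputation in section 2.20. The change should be recorded before the blinded analysis begins.

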**Methods:**

This will be a parallel‐group randomised controlled superiority trial. One‐hundred and forty community‐dwelling people with painful midfoot OA will be randomised to receive either arch contouring foot orthoses or flat sham inserts. Outcome measures will be obtained at baseline, 4, 8 and 12 weeks; the primary endpoint for assessing efficacy being 12 weeks. The primary outcome measure will be average midfoot pain whilst walking over the last 7 days on an 11‐point numerical rating scale. Secondary outcome measures include function (walking/standing subscale of the Manchester–Oxford Foot Questionnaire), participants' perception of overall treatment effect (self‐reported global rating of change on a 15‐point Likert scale), physical activity (Incidental and Planned Exercise Questionnaire), general health‐related quality of life (Short Form‐12 Version® 2.0), use of co‐interventions and adverse events.

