### Outcome measures

2.12

The primary outcome will be measured prior to allocation at baseline and at 12 weeks (the primary endpoint). All secondary outcomes unless stated otherwise will be measured prior to allocation at baseline and at 4, 8 and 12 weeks. Participants will complete online questionnaires at 4 week intervals, and they will be encouraged to contact the researchers at any time during the trial if needed. The outcome measures and associated timepoints are shown in Table 1.

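### The multiple-imputation model omits all week-4 and week-8 data, so it cannot correct bias from loss that depends on early response, and the complete-case check cannot reveal that bias

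*Protocol article*

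**What the plan says.** Section 2.20 gives a closed list of imputation predictors: "Multiple imputation will be used to replace any missing data using five iterations, with sex, age, baseline scores and group allocation as predictors". The analysis that follows is a 12-week ANCOVA "with baseline scores and intervention group entered as independent variables". The imputation model therefore holds sex, age and possibly other outcomes' baseline scores beyond what the ANCOVA already contains. Two sensitivity analyses address missing data: a complete-case analysis ("only analyse participants who provide outcome data") and "last observation carried forward". The same section applies no substitution to the GROC, co-interventions, adherence or adverse events.

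On what is collected between baseline and week 12, Section 2.12 says "All secondary outcomes unless stated otherwise will be measured prior to allocation at baseline and at 4, 8 and 12 weeks", and Section 2.16 records adherence at the three follow-up times. For pain the article disagrees with itself. The Abstract says "Outcome measures will be obtained at baseline, 4, 8 and 12 weeks", while Section 2.12 says "The primary outcome will be measured prior to allocation at baseline and at 12 weeks".

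**The concern.** Multiple imputation removes bias from missing outcomes only if loss is unrelated to the missing value given what the imputation model contains. In a 12-week trial of shoe inserts, early response is an obvious possible driver of loss: a participant with no relief by week 4 or 8 has less reason to complete the last questionnaire. Early scores are also likely to predict the 12-week score better than baseline does. The listed model contains neither.

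The primary estimate is at stake when early response drives loss differently in the two arms. The main safeguard is at stake too. If the complete-case analysis carries the same bias as the imputed one, agreement between them says nothing about it.

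**Working it through.** **1. Planning inputs.** Section 2.19 gives a difference of 1.1, SD 2.2, 80% power, alpha 0.05 (taken as two-sided), 1:1 allocation and 10% loss.

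n per arm = 2 x (1.960 + 0.842)^2 x (2.2/1.1)^2 = 2 x 7.85 x 4 = 62.8, so 63. Total 126; 126/0.9 = 140, as stated. (The t-based version gives 64 per arm and 128/0.9 = 142.2, so 143.) The sample size is not in question; these inputs carry into the next steps.

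**2. Why the stated imputation follows the complete-case result.** Suppose missing scores are drawn from a regression of week-12 pain on baseline and group fitted to completers. The imputed values then lie, on average, on the completers' own regression surface. Refitting the same ANCOVA to the completed data returns the completers' group coefficient plus imputation noise. Sex and age change this only as far as they relate to both loss and outcome.

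**3. Size, by simulation.** There were 3,000 trials per scenario, N = 140, SD 2.2, true effect -1.1 and five imputations. Assumptions not in the document:
- baseline-to-follow-up correlation 0.5
- early-to-week-12 correlation r = 0.75 (range 0.55 to 0.85)
- early effect about -0.8
- logistic dropout on the early score

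Bias in the week-12 difference, in points:

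| Loss depends on early score | Loss | r | Complete case | Stated imputation | With early score added |
|---|---|---|---|---|---|
| Alike in both arms | 10% | 0.75 | +0.030 | +0.031 | -0.003 |
| Active arm only | 10% | 0.55 | -0.070 | -0.069 | +0.018 |
| Active arm only | 10% | 0.75 | -0.146 | -0.146 | -0.001 |
| Active arm only | 10% | 0.85 | -0.165 | -0.165 | +0.006 |
| Opposite directions by arm | 10% | 0.75 | -0.230 | -0.230 | +0.004 |
| Alike in both arms | 20% | 0.75 | +0.057 | +0.059 | +0.001 |
| Active arm only | 20% | 0.75 | -0.241 | -0.241 | +0.014 |
| Opposite directions by arm | 20% | 0.75 | -0.447 | -0.449 | +0.005 |

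Simulation error on each bias is about 0.34/sqrt(3000) = 0.006. Complete case and stated imputation agree to within 0.002 in every row.

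Against the target at 10% loss: 0.03/1.1 = 3%; 0.07/1.1 = 6%; 0.23/1.1 = 21%. Against the standard error: 0.23/0.345 = 0.67.

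**4. Precision.** With 10% loss completely at random, the mean standard error is 0.340 for complete case, 0.345 for the stated imputation and 0.336 with the early score.

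**5. Where sex and age do help.** If loss depends on age in one arm and age correlates 0.1 to 0.3 with pain, complete-case bias of -0.049 to -0.087 becomes -0.015 to +0.012 under the stated model. If loss depends on early pain while age and sex also predict pain, the gain is slight: -0.155 becomes -0.144.

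**6. If pain is not measured at weeks 4 and 8.** Week-8 MOxFQ then stands in for early pain, with an assumed correlation of 0.5 or 0.7 between them (10% loss, active arm only).
- Loss depends on MOxFQ itself: stated-model bias of -0.084 or -0.106 becomes -0.005 or +0.001.
- Loss depends on unmeasured early pain: about -0.145 becomes -0.116 or -0.086.

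**7. Five imputations, if that is what is meant.** With about 10% missing information, between-imputation variance is roughly 0.10 x 0.345^2 = 0.012. Monte Carlo error is sqrt(0.012/5), about 0.05 points, or 0.14 of a standard error.

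**The case against.** The strongest reply is that harmful scenarios need dropout to behave differently in the two arms. Participants are blinded by limited disclosure (Section 2.8) and the sham was chosen for its credibility (Section 2.10.2), so similar dropout in both arms is at least as plausible. The bias is then about 0.03 points, under a tenth of a standard error. This stands, and it is why the size is given as a range. The direction is not fixed either: if high-pain participants leave the sham arm instead, the estimate moves towards no effect.

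A second reply is that the full remedy assumes interim pain scores, which Section 2.12 appears to rule out. This also stands. A reader might infer that data already collected would remove the bias entirely; step 6 shows that this depends on which reading of the schedule is right and on what drives loss.

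A reader might also infer that the planned imputation adds nothing over complete-case ANCOVA. That goes too far, because sex and age help when they drive loss (step 5).

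Third, last observation carried forward would use week-4 and week-8 pain if collected, so the plan does not wholly ignore such data. But that method rests on a strong assumption of its own, and if Section 2.12 is right it becomes baseline carried forward for the primary outcome.

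Finally, the plan restricts testing to week 12 to avoid serial testing. That reason does not reach the imputation model, where interim values serve as predictors and add no test.

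**Conclusion.** The point holds as a cheap improvement to a choice that the article fixes. When loss depends on early response, the stated imputation shares the bias of complete-case ANCOVA, and comparing the two cannot expose it. At the planned 10% loss the bias is about 0.03 points with dropout alike in both arms and about 0.07 to 0.23 points when it differs by arm. At 20% loss it reaches 0.45.

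These figures rest on assumed correlations and an assumed dropout model; the document gives neither. They do not show that the trial's result will be biased. A bias of a third of the target can be produced, but only with loss above the planned rate and opposite dropout patterns in the two arms. The imputation count is a minor matter: the article says iterations, which probably but not certainly means imputed datasets, and the pooled variance already allows for the extra noise.

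**What to change.** 1. Reconcile the Abstract with Section 2.12 on whether NRS pain is measured at weeks 4 and 8.
2. Add the available week-4 and week-8 values to the imputation model: those of the outcome being imputed where collected, and MOxFQ walking/standing in any case. Impute missing interim values jointly in the same model.
3. Treat adherence hours as optional. Section 2.20 applies no substitution to adherence, so using them would have to be squared with that rule.
4. State the number of imputed datasets in place of the five iterations, preferably well above five, with a fixed seed.
5. Keep the 12-week ANCOVA as planned.

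The cost is a sentence or two, settled before unblinded analysis, a slightly larger imputation model and a little more computing. If interim pain proves not to have been collected, the report should say that correction for loss driven by early pain is only partial.
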